#### Secondary outcomes

*Sedation efficacy outcomes*: (1) MOAA/S score after single administration; (2) time required to achieve a MOAA/S score of ≤ 3 points following single administration; (3) for patients not achieving adequate sedation depth after a single dose and documentation of additional medication doses and frequency; (4) total amount and number of additional administrations of remimazolam or propofol in both groups during the entire course of upper gastrointestinal endoscopy and treatment; (5) duration from the initiation of medication injection to the completion of upper gastrointestinal endoscopy and treatment; (6) type, frequency, and dose of alternative or additional remedial drugs required when the upper limit of supplementary dosage is exceeded; and (7) operator satisfaction.

*Consciousness recovery outcomes*: (1) Time to full awakening; (2) use of sedative antagonist flumazenil, if applicable; (3) assessment of patients’ recall of upper gastrointestinal endoscopy and treatment process using the Brice questionnaire (Appendix 4) after awakening; (4) duration of patients’ recovery; and (5) overall patient satisfaction.

*Safety outcomes*: (1) Incidence of hypertension or hypotension during the procedure and in the recovery room, (2) incidence of tachycardia or bradycardia during the procedure and in the recovery room, (3) incidence of low oxygen saturation during the procedure and in the recovery room, (4) airway intervention rate during the procedure and in the recovery room, (5) incidence of coughing within 1 min after endoscope insertion, (6) incidence of coughing during upper gastrointestinal endoscopy and treatment, and (7) incidence of injection-related pain.

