#### Efficacy evaluation{20a}

Primary endpoint evaluation: In the intention-to-treat (ITT) analysis population, a chi-square test will be used to compare the success rates of patients completing endoscopic examination and treatment between the two groups. Simultaneously, a generalized linear model will be employed to calculate the unadjusted and adjusted absolute risk differences (ARD). Adjusted variables will encompass stratification indicators (invasive procedures during upper gastrointestinal endoscopy and treatment), BMI, age, concurrent respiratory diseases, concurrent cardiovascular and cerebrovascular diseases, liver and kidney function abnormalities, and operator experience. Secondary effect sizes will be presented as odds ratios (OR) with a 95% confidence interval.

Evaluation of secondary endpoints: For the intention to treat (ITT, includes all participants who were randomly assigned, regardless of whether they completed the entire study or fully adhered to the study protocol) population, chi-square test or *t*-test will be employed for comparative analysis based on variable nature (e.g., categorical variables like low oxygen saturation, hypotension, tachycardia, intraoperative awareness, recovery delay, or continuous variables such as MOAA/S, NIBP, HR, and SpO_2_). Results will be reported as odds ratios (OR) and 95% confidence intervals using a generalized linear model. Time event variables (e.g., time to achieve a MOAA/S score of ≤ 3 points after a single dose) will be analyzed using Cox regression to describe and compare the two groups, generate Kaplan-Meier curves, express results as hazard ratios (HR), and report a 95% confidence interval.

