#### Exploratory analysis {20b}

Subgroup analyses based on patients’ clinical characteristics will be performed in pre-specified post hoc exploratory analyses. Potential factors impacting the examination success rate include BMI, age, the presence of respiratory diseases, cardiovascular and cerebrovascular diseases, liver and kidney dysfunction, alcohol and drug dependence, and operator experience.

Repeated measurement data (e.g., multiple measurements of MOAA/S, NIBP, HR, and SpO_2_) will be analyzed using a generalized additive mixed model (GAMM). The fixed effect will be a stratification indicator (invasive procedures during upper gastrointestinal endoscopy and treatment), and the interaction between groups and time will be evaluated.

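### The secondary analysis assigns odds ratios to every outcome that is not time-to-event, including the continuous ones compared by t-test, for which an odds ratio is not defined

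*Protocol article*

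**What the plan says.** All of this is in the protocol article.

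- **Test.** Efficacy evaluation {20a}, in the paragraph on secondary endpoints, offers a chi-square test or a t-test: "test will be employed for comparative analysis based on variable nature". Low oxygen saturation and hypotension are among its categorical examples. The second class is introduced as "or continuous variables such as MOAA/S, NIBP, HR, and SpO_2".
- **Effect measure.** The next sentence reads "Results will be reported as odds ratios (OR) and 95% confidence intervals using a generalized linear model". It is not limited to the categorical class.
- **Time-to-event variables.** The sentence after that uses Cox regression for these, and the plan will "express results as hazard ratios (HR), and report a 95% confidence interval".
- **Repeated measurements.** Exploratory analysis {20b} says that serial MOAA/S, NIBP, HR and SpO2 values "will be analyzed using a generalized additive mixed model (GAMM"), with a group-by-time interaction. It names no effect measure.
- **Descriptive summaries.** General principles {20a} gives means with standard deviations or medians for continuous variables. These describe the data and are not between-group estimates.
- **Outcomes.** Secondary outcomes contains binary items, such as "Incidence of hypertension or hypotension during the procedure and in the recovery room", and non-binary ones, such as "total amount and number of additional administrations of remimazolam or propofol in both groups". It also lists operator and patient satisfaction, each scored 0 to 10 according to the data collection sections.

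**The concern.** The plan varies its effect measure by type of variable: it separates out time-to-event outcomes and gives them hazard ratios. Continuous outcomes get their own test but share the odds ratio with the categorical ones. For them, the stated test and the stated estimate do not belong together.

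At stake is the reporting of outcomes that bear directly on the trial's aims. The objectives concern patient comfort and good conditions for the endoscopist, and the two satisfaction scores measure these most directly. An analyst who reaches them finds a rule that cannot be carried out and must depart from it. The plan does not say how, so the choice of scale would be made without a pre-specified basis. The article describes the outcome assessors as unblinded (Who will be blinded {17a}), so it is better not to leave that choice open.

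**Working it through.** The plan gives no figure on this point. The check sets its passages against what each effect measure requires.

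**Step 1: what each measure needs.**

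- Odds ratio: [p1/(1 − p1)] ÷ [p0/(1 − p0)], where p is the probability of an event in each arm. The outcome must be binary. An ordinal outcome can carry a common odds ratio if a proportional-odds model is specified.
- t-test: compares the two arm means. The matching estimate is mean1 − mean0, in the units of the outcome.
- Generalized linear model: the measure depends on family and link. Binomial with logit link gives an odds ratio; Gaussian with identity link gives a mean difference. The plan fixes neither family nor link, but it does fix the output as an odds ratio.

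**Step 2: illustration.** On simulated data with assumed means of 120 and 125, SD 15 and 261 patients per arm, a Gaussian identity-link model returned a difference of 7.0 (95% CI 4.6 to 9.3). That is a mean difference, and no odds ratio comes out of the model. A binomial-logit model fitted to the same raw values gave coefficients of the order of 10^16 to 10^17, which mean nothing.

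**Step 3: apply the rule to the listed outcomes.** Secondary outcomes has 7 sedation, 5 recovery and 7 safety items, 19 in all. The classification is mine.

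| Type | Items | Count | Measure under the plan | Fits? |
|---|---|---|---|---|
| Binary | 7 safety incidences or rates, flumazenil use, recall | 9 | Odds ratio | Yes |
| Times and durations | Time to MOAA/S ≤ 3, drug start to end of procedure, time to full awakening, duration of recovery | 4 | Hazard ratio, if all are treated as time-to-event | Yes |
| Score, count or amount | MOAA/S after single dose, additional doses when the first was inadequate, total amount and number of additional doses, alternative or remedial drugs, operator satisfaction, patient satisfaction | 6 | Odds ratio | Not as written |

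9 + 4 + 6 = 19. Two of the six need a note. MOAA/S is ordinal and could carry an odds ratio from an ordinal model, but the plan calls it continuous and names no such model. The remedial-drug item is mixed: whether any was used is binary, but frequency and dose are not.

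**Step 4: is another measure named elsewhere?** General principles {20a} is descriptive. Exploratory analysis {20b} names a model but no measure, and covers repeated measurements only. No between-group measure for continuous outcomes appears in the article.

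**Step 5: does it reach the primary analysis?** The primary outcome is binary success or failure, with an absolute risk difference and a supplementary odds ratio, both of which are defined. The sample size rests on 79% success, a margin of 0.10, one-sided α of 0.025 and power of 0.80: (1.960 + 0.842)² × 2 × 0.79 × 0.21 ÷ 0.10² = 260.4, so 261 per arm and 522 in total, as stated. No secondary-outcome quantity enters.

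**The case against.** The best defence is that the sentence was meant for categorical endpoints and lost its qualifier when the text was condensed. A generalized linear model with an identity link would give the mean difference, and effect measures for individual continuous outcomes are commonly left to the analysis plan. The intention is plausible, and the mere absence of a mean difference would not be a finding. But the article does name a measure, in an unrestricted sentence directly after one that lists continuous variables. That is a stated rule that does not fit its stated test.

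Four stronger readings are tempting, and the document does not support them.

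- *Every secondary result is an odds ratio.* Time-to-event outcomes receive hazard ratios.
- *The blood pressure, heart rate and oxygen saturation outcomes are all mis-specified.* Secondary outcomes lists them as incidences, for which an odds ratio is valid. The mismatch touches them only where Efficacy evaluation {20a} lists them as continuous.
- *The analyst would exponentiate a mean difference or choose a cut-point after unblinding.* The plan proposes neither. Figures such as exp(5) = 148 for a 5 mmHg difference illustrate an operation nobody has planned, and the article describes the analysts as blinded to participants' identities.
- *Odds ratios are wrong for the binary secondary outcomes.* They are legitimate. Risk differences, to match the primary outcome, would be a preference.

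**Conclusion.** The point holds as a specification error in the secondary analyses. Read literally, the rule cannot be applied to about 6 of the 19 listed secondary items, nor to NIBP, HR and SpO2 as continuous variables. The count assumes that all four times and durations fall under the Cox rule and that MOAA/S is analysed as continuous, as the plan says. Any duration compared by t-test instead would add to the six; an ordinal model for MOAA/S would remove one.

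No number in the plan changes. The primary non-inferiority comparison, its margin and the sample size are untouched, and there is no bias or loss of power to quantify. The correction should still be made before analysis, because the affected outcomes include both satisfaction scores.

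**What to change.** Replace the unrestricted sentence with one rule per type of outcome:

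- **Binary secondary endpoints:** odds ratio with 95% CI, as now.
- **Continuous secondary endpoints:** mean difference with 95% CI from an identity-link model that includes the randomisation stratum (planned invasive treatment). Take the p-value from the same model so that test and interval agree. If the distribution is skewed, as dose counts may be, report a median difference with 95% CI and a matching rank-based test.
- **MOAA/S:** either the mean difference, or, if an odds ratio is wanted, a common odds ratio from a proportional-odds model named in the plan.
- **Time-to-event endpoints:** hazard ratio, as now, with a list of which times and durations fall under this rule.

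The essential change is the measure for continuous endpoints; including the stratum is good practice. One detail for the total amount of study drug: the arms receive different drugs at initial doses of 1.5 and 0.15 mg/kg, so a between-arm difference in milligrams says little. Describing the amount by arm and comparing the number of additional administrations avoids this.

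The cost is a few sentences in the analysis plan. Data collection, sample size and software stay the same.

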### Interventions {11a}

Upon obtaining signed informed consent from the subject, the following process is executed (Figs. 2 and 3):Screening periodAfter the patient enters the endoscopy examination room and decides to undergo upper gastrointestinal endoscopy treatment, the researcher collects information on the patient’s demographics, medical condition, and proposed examination plan. An independent anesthesiologist evaluates the patient’s examination plan before randomization, and eligible patients are selected based on the inclusion/exclusion criteria. Patients should be assessed by researchers who are knowledgeable about the protocol and authorized to do so in a quiet environment. The study’s purpose, methods, potential benefits, and risks must be thoroughly explained to the patient and/or their representative, and data collection and follow-up procedures before, during, and after the examination must be detailed.The researchers should address the patient and their family members’ questions in detail, allowing sufficient time for consideration and obtaining informed consent from the patient and/or their representative on a completely voluntary basis. The assessor must not be involved in the patient’s examination, sedation, or anesthesia management plan. *Sedation management plan*: An anesthetist with the title of attending physician or above will implement the sedation and anesthesia plan. The patient enters the endoscopy consultation room’s preparation area and takes 10 g of lidocaine gel (containing 0.2 g of lidocaine) orally 5 min before the examination. The patient assumes a left lateral position on the treatment bed in the endoscopy consultation room, and basic vital signs including noninvasive blood pressure (NIBP) of the right upper arm, electrocardiogram, and pulse oxygen saturation (SpO_2_) are monitored. Oxygen is continuously administered through a 4L/min nasal cannula throughout the procedure until the patient fully awakens. A venous line is established, and sufentanil 5 μg is administered intravenously. Patients scheduled for upper gastrointestinal endoscopy are randomized to receive one of two sedative drug infusions: propofol in group C or remimazolam in group R. In group C, patients receive a single dose of propofol at 1.5 mg/kg, while in group R, patients receive a single dose of remimazolam at 0.15 mg/kg, both administered within 1 min. According to the domestic expert consensus, moderate or deep sedation is required for upper gastrointestinal endoscopic examination. Therefore, the MOAA/S score (Appendix 2) should be assessed 1 min after propofol injection. If the MOAA/S score is greater than 3 points, propofol 0.5 mg/kg or remimazolam 0.05 mg/kg should be administered repeatedly until the MOAA/S score is less than or equal to 3 points, with a maximum of five repetitions. The VAS (Appendix 3) should be assessed during propofol or remimazolam injection.*Intraoperative monitoring*: Intraoperative monitoring includes electrocardiogram, noninvasive blood pressure, pulse oxygen saturation, and, when necessary, body temperature, urine output, end-tidal carbon dioxide concentration, and blood glucose levels.*Sedation maintenance plan*: During the examination procedure, the chief anesthesiologist determines whether to administer additional trial medication based on the surgical process and duration. Propofol (0.5 mg/kg) or remimazolam (0.05 mg/kg) is administered in single doses with a minimum interval of 1 min to maintain the patient at an appropriate level of sedation (MOAA/S score ≤ 3). If sedatives are insufficient to maintain appropriate sedation during the examination, the investigator may decide to use alternative sedative agents (midazolam).*Examination plan*: Based on the type of lesion, the endoscopic examination of the upper digestive tract in our hospital may include, but is not limited to, upper gastrointestinal inflammation, tumors, ulcers, polyps, gastroesophageal varices, and gastrointestinal strictures. According to the type of endoscopic treatment of the upper gastrointestinal tract, it may include, but is not limited to, sclerotherapy, argon plasma coagulation, high-frequency electrocautery, and submucosal dissection. Various procedures are conducted following established clinical surgical protocols. *Postoperative management plan*: After the examination or procedure, the patient enters the anesthesia recovery room, where continuous monitoring of ECG, noninvasive blood pressure, and oxygen saturation occurs. The MOAA/S score is assessed every 5 min. Once the score reaches 5 points for three consecutive assessments, and blood pressure, heart rate, and oxygen saturation are normal and stable, the patient can leave the recovery room accompanied by a companion. In case of special circumstances, refer to the adverse event handling procedures.

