#### Intraoperative data collection

Starting from the administration of intervention drugs, test the MOAA/S score every 30 s for 5 min, and then test every 2 min until the examination and operation are completed.

Record the time interval (seconds) from the start of intervention drugs to the time when MOAA/S score ≤ 3.

Record the presence of injection pain during the administration of intervention drugs using a visual analog scale (VAS) ranging from 0 to 10, where 0 indicates no pain and 10 indicates maximum pain (see Appendix 3). This assessment is conducted 1 min and 20 min after the start of drug administration or every 5 min thereafter if the patient remains sedated until the patient can complete the scale.

Record the MOAA/S score when the endoscope is smoothly placed in the esophagus.

Record the dose of intervention drugs used when the endoscope is smoothly inserted into the esophagus (including additional and rescue drugs, types, frequency, and dosage).

Measure NIBP every 3 min from the start of intervention drugs until the end of the examination.

Continuously monitor SpO_2_ until the end of the examination and record the minimum SpO_2_ during the procedure.

Record the total duration of the examination and operation (in minutes).

Record the types, frequency, and dosage of additional or rescue drugs during the examination, along with the corresponding time points.

Record the number of interruptions during the examination and the reasons for interruption, along with the time elapsed since drug administration began.

Record adverse events and their corresponding times during the period from drug administration to the end of the examination (see 1.10), such as respiratory spasms, reflux aspiration, coughing during endoscope entry into the oral cavity, SpO_2_ below 90% due to repeated coughing, SpO_2_ below 90% due to respiratory depression, positive pressure mask ventilation, jaw support-assisted ventilation, systolic blood pressure < 80 mmHg, or the need for vasopressors, systolic blood pressure ≥ 180 mmHg, *HR* ≤ 55 beats/min, *HR* > 100 beats/min, and the frequency and conditions of severe arrhythmias.

Operator satisfaction score (0–10 points, with 0 indicating very dissatisfied and 10 indicating very satisfied).

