#### Statistical software

All analyses were performed with the R software (version 3.4.3, R Foundation for Statistical Computing, and Empower Stats, X&Y Solutions Inc., Boston, MA, USA).

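### Time to MOAA/S ≤ 3 is read on a 30-second grid but analysed with ordinary Cox regression; if the arms differ, ties pull the hazard ratio towards 1 by an amount the protocol leaves open

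*Protocol article*

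**What the plan says.** All references are to the Protocol article.

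- **Outcome.** Secondary outcomes lists, under sedation efficacy, the "time required to achieve a MOAA/S score of ≤ 3 points following single administration".
- **Reading schedule.** Intraoperative data collection says: "Starting from the administration of intervention drugs, test the MOAA/S score every 30 s for 5 min, and then test every 2 min". That allows at most 10 readings in the first 5 min.
- **Recording.** The same section says: "Record the time interval (seconds) from the start of intervention drugs to the time when MOAA/S score ≤ 3".
- **Dosing and first decision.** Under Interventions {11a} the first doses are "both administered within 1 min", and "the MOAA/S score (Appendix 2) should be assessed 1 min after propofol injection". The top-up decision therefore comes at about 120 s from the start of drug, after scheduled readings at 30, 60, 90 and 120 s.
- **Analysis.** Efficacy evaluation {20a} says: "time to achieve a MOAA/S score of ≤ 3 points after a single dose) will be analyzed using Cox regression". Kaplan-Meier curves and an HR with 95% CI are to be reported. No tie method or grouped-time method is named, and Statistical software does not settle it.

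**The concern.** Whether a score has reached 3 or below can be known only when the scale is tested. Writing the interval in seconds does not add resolution that the 30-s schedule lacks. Many patients will therefore share the same onset time, and a large part of those still at risk may reach the threshold at one reading.

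The Cox partial likelihood is built for continuous times with few ties. Under heavy ties the usual approximations (Breslow, Efron) bring the HR closer to 1 than the hazard ratio of the underlying process, and the CI is then centred in the wrong place. At stake is the reported size of any difference in onset speed, a named efficacy outcome: the two drugs could look more alike in onset than they are.

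**Working it through.** **Inputs.** From the document: the 30-s grid to 300 s and 288 per group (Sample-size calculation). The document gives no figure for this endpoint to reproduce and no expected onset distribution. Assumed: Weibull onset with reference-arm median 60 s, shape 2, 3 or 5 (coefficient of variation 52%, 36%, 23%), and true HR 0.67 or 0.50.

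**Step 1: why ties shrink the HR.** Take median 60 s, shape 3, HR 0.50. Survival (not yet at MOAA/S ≤ 3) is S0(t) = 0.5^((t/60)^3) in the reference arm and S1(t) = S0(t)^0.50 in the other. The probability of reaching the threshold at a reading, among those still at risk, is h = 1 − S(this reading)/S(previous reading). At 60 s: h0 = 1 − 0.500/0.917 = 0.455 and h1 = 1 − 0.707/0.958 = 0.262.

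| Reading | h0 | h1 | h1/h0 | ln(1−h1)/ln(1−h0) | Share of all patients |
|---|---|---|---|---|---|
| 30 s | 0.083 | 0.042 | 0.51 | 0.50 | 6% |
| 60 s | 0.455 | 0.262 | 0.58 | 0.50 | 33% |
| 90 s | 0.807 | 0.561 | 0.70 | 0.50 | 40% |
| 120 s | 0.959 | 0.799 | 0.83 | 0.50 | 17% |

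The ratio of per-reading probabilities drifts towards 1 as h grows. The complementary log-log contrast in the fifth column equals the true HR at every reading. Breslow ties in effect average the fourth column, and Efron ties correct most of this but not all. The large-sample limits here are 0.658 (Breslow) and 0.543 (Efron).

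**Step 2: size at 288 per arm** (simulation, median 60 s; coverage of the true HR by the 95% CI in brackets; a range is two separate simulations).

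| True HR | Shape | Efron | Breslow |
|---|---|---|---|
| 0.67 | 2 | 0.68 (94%) | 0.75 (81%) |
| 0.67 | 3 | 0.71 (93%) | 0.79 (51%) |
| 0.67 | 5 | 0.78 (59%) | 0.86 (4%) |
| 0.50 | 2 | 0.52 (about 95%) | 0.60 |
| 0.50 | 3 | 0.54 (81–86%) | 0.66 (6%) |
| 0.50 | 5 | 0.64 (12–14%) | 0.76 (0%) |

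The grouped-time complementary log-log model returned 0.66–0.67 and 0.49–0.50, with coverage of 92–97% across the runs.

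**Step 3: what drives it.** A separate simulation used 261 per arm. With median 75 s, shape 2.5 and follow-up cut at 120 s there are only four distinct values, yet Efron gives 0.51 for a true 0.50 with about 95% coverage (Breslow 0.58, 69%). With median 45 s, shape 3 and 300 s follow-up there are again about four values, and Efron gives 0.57 with 74% coverage. The count of values is therefore not decisive. What matters is how large a fraction of those at risk reach the threshold at one reading.

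**Step 4: no true difference.** At HR 1 the estimate is unbiased. The rejection rate is 1.7–5.0% with Efron and 0–2.2% with Breslow, against a nominal 5%.

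**The case against.** The strongest case against has five parts.

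- **The damage is conditional.** With Efron ties and moderate spread (median 60 s shape 2, or 75–90 s shape 3) the HR is off by about 2–7% with 92–95% coverage. A reader might infer that Cox regression here gives an invalid 95% CI as such. The document does not support that, because serious under-coverage needs Breslow ties or a tight or early onset, and it states neither. This stands.
- **Tie handling is commonly left to the analysis plan**, which is not shown. That stands for the missing tie option, which is not itself a fault. It does not cover the model, which the article fixes, and in the tight-onset settings the better correction also misses.
- **The bad cases are small shifts.** Under the Weibull model the ratio of medians is (1/HR)^(1/shape). Against 60 s, HR 0.67 at shape 5 means about 65 s, HR 0.50 at shape 5 about 69 s, and HR 0.50 at shape 3 about 76 s. All lie within one reading interval. The test result also survives: ln(0.78)/0.085 is about −2.9. This limits clinical importance but not the error in the reported HR.
- **The number of distinct values cannot be read from the document.** A reader might infer four to eight. The grid allows up to 10 in 5 min, the runs gave from about 4 to 10, and the assessment 1 min after injection need not fall on the grid. Four follows only if time is cut at the top-up decision.
- **The endpoint is secondary and has no margin.** A reader might infer that the non-inferiority conclusion is biased towards success. It is not: the 10% margin and the 576 patients belong to the composite primary outcome.

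**Conclusion.** The mismatch between the reading schedule and the stated model is real, and the direction of any bias is clear: towards 1 when the arms differ. The size is uncertain. For a true HR of 0.50 it runs from negligible (0.52, about 95% coverage) to severe (0.64, 12–14%) under Efron ties, and from 0.60 to 0.76 under Breslow. These figures rest on an assumed Weibull onset with proportional hazards, a 60-s reference median and 288 per arm. The document supplies no onset distribution against which to choose among them. There is no false-positive risk, and the primary analysis and sample size are unaffected. This is a minor point, worth making because the remedy is nearly free.

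**What to change.** In Efficacy evaluation {20a}, replace Cox regression for time to MOAA/S ≤ 3 with a grouped-time proportional-hazards model: a discrete-time binomial model with complementary log-log link, one term per reading interval, treatment group and the randomisation stratum. The equivalent interval-censored proportional-hazards model would also serve. Keep the HR with 95% CI as the reported effect. At minimum, specify Efron ties, not Breslow, with the grouped-time model as a check. Also report, by arm, the proportion with MOAA/S ≤ 3 at each scheduled reading.

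Cost: one sentence and a standard generalized linear model in the R software already named, with no new data or patients. The CI becomes wider. The standard error of the log HR was 0.087–0.114 in the scenarios run, against about 0.085 for Cox, which is 2% to 34% larger (0.087/0.085 = 1.02; 0.114/0.085 = 1.34), and the gap is wider when onset is tight.
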